|          |                                                                                                                                                                                  | (all participants in the EarlyCDT-positive group will be approached with the recruitment aim of 300 from this group collected at 1,3,6,12,18 and 24 months. The EarlyCDT-negative and control groups will be recruited at the same rate as the EarlyCDT-positive group with the recruitment aim of 300 from each group collected at 1,3,6 and 12 months). |
| 6 | to assess the effectiveness of EarlyCDT-Lung test on other clinical outcomes such as CVD, COPD, other cancers, hospital stays and outcomes identified through SMR linkage, etc.; | Incidence of other clinical outcomes such as CVD, COPD, other cancers, hospital stays, identified through SMR linkage, measured at 24 months, 5 and 10 years in the intervention arm and in the control arm; assessment of significance of differences;                                                                                                   |
| 7 | to assess uptake of subsequent investigations such as CXR, CT, bronchoscopy, etc.                                                                                                | numbers in all groups (EarlyCDT-Lung test-positive, EarlyCDT-Lung test-negative, control) undertaking subsequent investigations such as CXR, CT, bronchoscopy, etc.                                                                                                                                                                                       |

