(6) incidence at 24 months, and after 5 years and 10 years, in other clinical measures such as CVD, COPD, hospital stays, and outcomes identified through SMR linkage, etc. in the intervention arm and in the control arm; assessment of significance of differences;

(7) numbers in all groups (EarlyCDT-Lung test-positive, EarlyCDT-Lung test-negative, control) undertaking subsequent investigations such as CXR, CT, bronchoscopy, etc.

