6) incidence at baseline, 24 months, and after 5 years and 10 years, in other clinical measures such as CVD, COPD, other cancers, hospital stays, and outcomes identified through SMR linkage, etc. in the intervention arm and in the control arm; assessment of significance of differences;

7) numbers in all groups (EarlyCDT-Lung test-positive, EarlyCDT-Lung test-negative, control) undertaking subsequent investigations such as CXR, CT, bronchoscopy, etc.

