| Inclusion/Exclusion Criteria                                                                                            | X                       |                                                                                                                     |                      |                                                                                                                                                                              |           |
| 

Review/Record only Relevant Medical History relating to IC/EC

           | X                       |                                                                                                                     |                      |                                                                                                                                                                              |           |
| 

Review/Record Relevant Medications

Relating to IC/EC

     | X                       |                                                                                                                     |                      |                                                                                                                                                                              |           |
| Blood Sample                                                                                                            | X                       |                                                                                                                     |                      |                                                                                                                                                                              |           |
| Baseline Questionnaire                                                                                                  | X                       |                                                                                                                     |                      |                                                                                                                                                                              |           |

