### 3.3 EXCLUSION CRITERIA

1. History of any cancer other than non-melanomatous skin cancer, cervical cancer in situ.
2. Symptoms suggestive of lung cancer within past 6 months (haemoptysis, unintentional weight loss (at least 5% in preceding 6 months).
3. Patients for whom the GP considers invitation to the study would cause undue distress.
4. Patients with other terminal disease.
5. Patients on prolonged / continuous use (> 3months) of cytotoxic/ immuno-suppressant drugs eg: Methotrexate, Cyclophosphamide, Azathioprine, Rapamycin, Mycophenolate, Rituximab and anti-immunophilins such as Ciclosporin, Tacrolimus. Monotherapy using glucocorticoids/ steroids eg prednisolone is NOT an exclusion criteria.

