## **7.2 PROPOSED ANALYSES**

Characteristics of participants will be compared informally between treatment arms at baseline. The main analysis of the primary outcome will be intention-to-treat. Cox proportional hazards models will be used to estimate the hazard ratio of the rate of late stage lung cancer in the intervention arm compared to the control arm.

Participants who are lost to follow up will be censored. The models will adjust for age, gender smoking history and practice. If appropriate, random cluster effects will be included rather than fixed effects for practices. A similar methodology will be used for the secondary outcomes of comparisons of mortality rates (secondary outcomes 3a and 3b). A subsequent analysis will compare the outcomes of those with EarlyCDT positive in comparison to those in the intervention group with EarlyCDT negative (primary contrast for this analysis) and those in the control group (secondary analysis 1). Comparisons of proportions (secondary analyses 1 and 4) will be carried out using chi square tests. Fishers exact test will be used if the numbers of events are small.

The analyses of the questionnaire responses (secondary analysis 5) will be carried out using the appropriate 2 sample t tests and regression methods at baseline. Non parametric tests will be used if there is evidence of non-normal scores. Multilevel models will be used to analyse the repeated scores during follow up.

Poisson regression models, adjusting for follow up time if necessary, will be used to investigate the other clinical measures (secondary outcomes 6 and 7).

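### Section 1.5.2 defines outcome 6 as incidence at baseline, in conflict with both other definitions, leaving room to count existing CVD or COPD; its Poisson model names no adjustment except follow-up time

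*Protocol*

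**What the plan says.** The protocol defines outcome 6 in three places.

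- Section 1.5.2, item 6: "incidence at baseline, 24 months, and after 5 years and 10 years, in other clinical measures such as CVD, COPD", extended to other cancers, hospital stays and linked outcomes, in both arms, with the significance of differences to be assessed.
- Summary, secondary outcome 6: "incidence at 24 months, and after 5 years and 10 years, in other clinical measures such as CVD, COPD, hospital stays". There is no baseline time point.
- Summary table of objectives and outcomes, row 6: "identified through SMR linkage, measured at 24 months, 5 and 10 years in the intervention arm and in the control arm". Again there is no baseline.

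Section 7.2 gives the analysis: "Poisson regression models, adjusting for follow up time if necessary, will be used to investigate the other clinical measures". It names no other covariate for this outcome. The same section says that participant characteristics are compared informally between arms at baseline, and it adjusts the primary Cox model for age, gender, smoking history and practice. Section 4.5 stratifies randomisation by site and minimises on age, sex and smoking history.

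On who can enter, Section 3.3 excludes "History of any cancer other than non-melanomatous skin cancer, cervical cancer in situ"; CVD and COPD are not on the list. Table 1 in Section 2.4 limits history-taking at Visit 1 to eligibility: "Review/Record only Relevant Medical History relating to IC/EC". Section 6.1, however, makes GP and hospital notes source data for relevant past history and admissions.

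**The concern.** There is no incidence at the moment of randomisation. What can be measured then is how many people already have the condition. If a quantity called incidence is to be reported at baseline and then under the same name at 24 months, 5 years and 10 years, one natural reading is a cumulative count of everyone with the diagnosis on record. At follow-up that count is existing disease plus new disease.

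Smokers aged 50 to 75 can enter with CVD or COPD, and Section 5.1 expects co-morbidity in this population. Existing disease is spread evenly over the arms by randomisation, but adding the same number to both numerators still pulls their ratio towards 1 and lowers power. Research question iii in Section 1.2, on whether the test improves CVD, COPD and hospital stays, rests on this outcome. An effect on new disease could be masked and the result reported as no difference.

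A second, separate point is that the outcome 6 model leaves out the factors used to randomise, as well as prior disease and admissions, which should predict these outcomes.

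**Working it through.** **1. The definitions side by side.**

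| Place | Time points for outcome 6 |
|---|---|
| Section 1.5.2 | baseline, 24 months, 5 and 10 years |
| Summary | 24 months, 5 and 10 years |
| Summary table | 24 months, 5 and 10 years |

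Two of the three omit baseline. Taken literally, the significance clause in 1.5.2 also covers baseline, which does not fit the informal baseline comparison in 7.2.

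**2. What happens if existing disease is counted.** The protocol states no event rate, effect or power for outcome 6, so there is no figure to reproduce. The only input from the protocol is 5,000 per arm (Section 7.1). Everything else here is assumed: prevalence p at entry of 5% to 30%, incidence i in the disease-free of 3% to 10%, and a true risk ratio of 0.80 for new disease.

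Observed ratio = [p + (1 − p) × i × 0.80] / [p + (1 − p) × i]

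Example with p = 10% and i = 5%: control 0.10 + 0.90 × 0.05 = 0.145; intervention 0.10 + 0.90 × 0.04 = 0.136; ratio 0.136 / 0.145 = 0.94.

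Power is for two proportions, two-sided 5%: 5,000 per arm if existing disease is counted, 5,000 × (1 − p) per arm if only new disease in the disease-free is counted.

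| i | p | Ratio, existing disease counted | Power, existing counted | Power, new disease only (ratio 0.80) |
|---|---|---|---|---|
| 3% | 20% | 0.98 | 8% | 38% |
| 5% | 10% | 0.94 | 25% | 63% |
| 5% | 20% | 0.97 | 15% | 58% |
| 10% | 10% | 0.91 | 65% | 91% |
| 10% | 20% | 0.94 | 44% | 88% |
| 10% | 30% | 0.96 | 31% | 83% |

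Over the whole assumed range, 0.80 would be observed as 0.87 (p = 5%, i = 10%) to 0.99 (p = 30%, i = 3%). With no true effect the ratio stays at 1 either way.

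**3. Is a 20% reduction across the arm plausible?** Sections 4.7 and 8.7.4 expect 400 to 450 positive tests, and only these participants are imaged: 450 / 5,000 = 9% of the arm. If the effect runs only through that pathway, and test-positives carry average risk, preventing every new case among them would give a ratio of 0.91. At i = 10% and p = 20%, power is then about 28% counting new disease only and 12% counting existing disease as well. The power gaps in the table are therefore an upper illustration.

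**4. Does leaving baseline disease out of the Poisson model attenuate the ratio?** Suppose 20% have disease at entry and have events at four times the rate of the others (0.20 against 0.05), with a common ratio of 0.80. Control: 0.80 × 0.05 + 0.20 × 0.20 = 0.080. Intervention: 0.80 × 0.04 + 0.20 × 0.16 = 0.064. Unadjusted ratio: 0.064 / 0.080 = 0.80. With a log link and randomised arms, the omission does not bias the ratio. Its cost is precision.

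**The case against.** The strongest case against is that the documents establish only a misplaced word. All three definitions use the term incidence, which ordinarily means new cases. A Poisson model with follow-up time suggests event rates after randomisation, not cumulative proportions with the diagnosis. Baseline in 1.5.2 may mean no more than a baseline description. At-risk sets, look-back periods and code lists for a secondary outcome usually go in the SAP, which is not at hand, and Section 6.2 refers tables for the secondary outcomes to it. The notes named in Section 6.1 would allow old and new disease to be separated.

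Much of this stands. A reader might infer that the protocol counts existing disease as outcome. It does not say so anywhere. The nearest text, in Section 5.1, regards known progressions and co-morbidities as outcomes, but it explains safety recording and does not define a numerator. A reader might also infer that the Poisson model causes dilution by omitting baseline disease; step 4 of the working shows that it does not. Nor is a baseline significance test clearly planned: the clause on significance is a general ending shared with outcomes 3a and 3b, and 7.2 points the other way.

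What the objection does not remove is that 1.5.2 states an impossible quantity and disagrees with the two other definitions. That is an error in the text, not detail left for later. Likewise, 7.2 does set out a model for outcome 6, with a shorter adjustment than the one it sets for the primary outcome.

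**Conclusion.** Outcome 6 is wrongly stated in Section 1.5.2 and should be reconciled with the Summary and the summary table. The wording leaves room for existing CVD or COPD to be counted at follow-up. If it were, the ratio would move towards 1 and power would fall. That consequence is conditional on how the outcome is derived, and its size cannot be given from the protocol: the ratios and power figures above rest on assumed prevalence and incidence and on a 20% effect that is hard to square with about 9% of the arm being imaged.

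The mechanism applies mainly to CVD and COPD. Prior cancer is largely excluded, so it hardly touches other cancers, and hospital stays after randomisation are counted events rather than prevalent conditions.

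The narrow adjustment in the Poisson model is a separate and lesser matter. It loses precision and does not bias the arm comparison. The point concerns a secondary outcome, and the correction is worth making before linkage data are extracted.

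**What to change.** 1. In Section 1.5.2, item 6, delete baseline from the list of time points so that all three definitions agree. State that baseline values are prevalence, used only for description or as covariates.
2. For CVD and COPD, define incidence as the first record dated after randomisation in participants with no such record in a fixed look-back of SMR or GP data.
3. In Section 7.2, adjust the outcome 6 models for age, sex, smoking history and site, the factors used in randomisation. For hospital stays, count admissions after randomisation and also adjust for the pre-randomisation count over the look-back.

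The cost is a few sentences in 1.5.2 and 7.2 and a look-back period in the linkage extract already planned. The downside is a slightly smaller at-risk group for each diagnosis.

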## **2 STUDY DESIGN**

### **2.1 STUDY DESCRIPTION**

A randomised controlled trial involving 10,000 participants recruited through primary care and community based recruitment strategies in Scotland.

#### **2.1.1 Setting**

Initially, 60-80 general practices in the lowest quintile of deprivation in Scotland (from a total of 200 in that quintile) as measured by the quintiles of the Scottish Index of Multiple Deprivation (SIMD 2012). Subsequent recruitment will be attained through adverts, posters, flyers and community based interactions. Potential participants can either be seen at their participating GP practice or at the local clinical research centre, or other appropriate clinical location.

#### **2.1.2 Participants**

Adults aged 50 to 75 who are at risk of lung cancer will be eligible to participate.

These are defined as those who are, current or former cigarette smokers with at least 20 pack-years, or have a history of cigarette smoking less than 20 pack-years plus an immediate family history (mother, father, brother, sister, child) of lung cancer which gives an individual a personal risk similar to a smoking history of 20 pack years. Participants should be healthy enough to undergo pulmonary resection or stereotactic radiotherapy.

## 2.2 STUDY FLOWCHART

### GP Invitation Letter/Study Introduction via alternative Recruitment Strategy

#### POSITIVE RESPONSE

- Send/email full PIS/PIB to non-GP recruitment strategy participants
- Make or receive call from participant
- Discuss study/check screening eligibility & arrange appointment
- Sent/email appointment letter

*(all participants have opportunity to cancel appointment after reading full PIS)*

### VISIT 1 @ GP PRACTICE OR CLINICAL RESEARCH FACILITY (DUNDEE/GLASGOW) ~30-45MINS

- See Research Nurse (RN) and obtain Informed Consent
- Check inclusion/exclusion criteria
- Obtain 10ml blood sample (for EarlyCDT test (0.5mls)/cancer related medical research)
- invite to complete study questionnaire (with assistance, if required)
- Web based randomisation – group allocation
- Remind participants that they will receive results in 4 weeks (test group only)

### POST BLOODS TO UNIVERSITY OF NOTTINGHAM (UON)

- UoN process 10ml sample and send 0.5ml of test group sample to Omcimmune, Kansas, USA and store test and non-test blood for future cancer related medical research (with consent)

### EARLYCDT TEST RESULTS

RN obtains results via secure portal within 4 weeks of Visit 1

#### POSITIVE RESULT

Letter sent inviting participant to attend/call  
**Visit 2 @ GP/CRF (~30 -45 mins)**

- CXR/Study CT arranged
- Summary information given/posted to Participant (PIS 2)
- Participation & Results Letter sent to GP

#### NEGATIVE RESULT

- Results letter sent /offer to discuss with RN

#### 6 MONTHLY STUDY CT SCANS

- Participant given appointments to attend for Study CT scans every 6 months for 2 years. Research team call 2-4 days before CT appt.

### CXR & STUDY CT SCAN @ LOCAL HOSPITAL

- Participant attends for CXR
  - If CXR negative participant attends for CT scan
  - If CXR positive or suspicious participant informed to attend for NHS CT scan and seen by PI (Respiratory Physician) if required
- (if NHS pathway negative, participant remains in study pathway)*

#### CLINICALLY SIGNIFICANT

#### CXR/CT SCAN/ IMAGE INCIDENTAL FINDINGS

Results deemed clinically significant by review panel of radiologists/respiratory physicians or GPs will be followed up via NHS routine clinical care.  
**Mortality/Morbidity/hospitalisations collected as outcome data for ALL PARTICIPANTS.**

## **2.3 STUDY MATRIX**

### *Recruitment Via GP Practices*

Identify 200 GP practices out of approx 1000 (i.e. Q1, bottom quintile)

Of these 150 are in Tayside / GCC

Of these approach 80 – 100

Of these recruit 60 – 80

At each practice:

Identify patients satisfying Inclusion/Exclusion criteria

Approach 200 – 250 eligible patients / practice

Recruit 130 – 170 patients / practice

(60 – 80) practices x (130 – 170) patients/ practice  $\approx$  10,000 patients

### *Recruits, visits, samples*

10,000 (recruits, visits, samples)

in 10 months @ 4 days/ week @ 48 weeks/ year

= 10,000 (recruits, visits samples) in 160 days

$\approx$  63 (recruits, visits, samples) per day or 250 / week

## 2.4 STUDY ASSESSMENT AND NOTIFICATIONS

Table 1. Overview of Study Assessments/Notifications.

| ASSESSMENT/PROCEDURES                                                                                                          | TIMELINE* ( ± 2 weeks)  |                                                                                                                     |                      |                                                                                                                                                                              |           |
|--------------------------------------------------------------------------------------------------------------------------------|-------------------------|---------------------------------------------------------------------------------------------------------------------|----------------------|------------------------------------------------------------------------------------------------------------------------------------------------------------------------------|-----------|
|                                                                                                                                | Visit 1
(~30-45mins) |                                                                                                                     | Visit 2*
(~30mns) | 
➤ *EarlyCDT Positive Test Participants may visit or call.
 
➤ EARLY CDT Negative Test Participants may attend for further information/advice only.
 |           |
| Informed Consent                                                                                                        | X                       |                                                                                                                     |                      |                                                                                                                                                                              |           |
| Inclusion/Exclusion Criteria                                                                                            | X                       |                                                                                                                     |                      |                                                                                                                                                                              |           |
| 

Review/Record only Relevant Medical History relating to IC/EC

           | X                       |                                                                                                                     |                      |                                                                                                                                                                              |           |
| 

Review/Record Relevant Medications

Relating to IC/EC

     | X                       |                                                                                                                     |                      |                                                                                                                                                                              |           |
| Blood Sample                                                                                                            | X                       |                                                                                                                     |                      |                                                                                                                                                                              |           |
| Baseline Questionnaire                                                                                                  | X                       |                                                                                                                     |                      |                                                                                                                                                                              |           |
| Thank you letter to Control Group                                                                                       |                         | X                                                                                                                   |                      |                                                                                                                                                                              |           |
| EarlyCDT- Lung Test Result Letter                                                                                       |                         | X                                                                                                                   |                      |                                                                                                                                                                              |           |
| GP Results Letter & ICF copy (negative)                                                                             |                         | X                                                                                                                   |                      |                                                                                                                                                                              |           |
| Result Discussion/ Imaging Schedule                                                                                     |                         |                                                                                                                     | X                    |                                                                                                                                                                              |           |
| Provide PIS 2                                                                                                           |                         |                                                                                                                     | X                    |                                                                                                                                                                              |           |
| GP Result Letter & ICF copy (positive)                                                                              |                         |                                                                                                                     | X                    |                                                                                                                                                                              |           |
| EARLYCDT – Lung Test Positive Result Participants – Imaging Schedule                                                    |                         |                                                                                                                     |                      |                                                                                                                                                                              |           |
|                                                                                                                                | TIMELINE( ± 4 weeks)    |                                                                                                                     |                      |                                                                                                                                                                              |           |
|                                                                                                                                | 0                       | 6 months                                                                                                            | 12 months            | 18 months                                                                                                                                                                    | 24 months |
| CXR                                                                                                                     | X                       |                                                                                                                     |                      |                                                                                                                                                                              |           |
| CT Scan*                                                                                                                | X                       | X                                                                                                                   | X                    | X                                                                                                                                                                            | X         |
| *Scheduled every 6 months, if participant enters NHS clinical care pathway, subsequent study CTscans will be cancelled. |                         | Research team member will call 2-4 days before each scheduled CT scan to check health status and attendance. |                      |                                                                                                                                                                              |           |

